# 6 Hypotheses

## 6.1 Primary

In apprentices enrolled in the TDTP who are at-risk of absenteeism, drop-out or unemployment post-program completion, exposure to either the ICM^10^ or ICM^01^ models will be superior to the BCM model for reducing absenteeism (as determined by the number of absence-free days), drop-out (as determined by the proportion of apprentices completing the program), and unemployment (as determined by proportion employed at 24 months post-program completion).

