# 7 Objectives

## 7.1 Primary

1) To compare the effect of ICM^10^ and ICM^01^ versus BCM on reducing absenteeism in apprentices enrolled in TDTP

2) To compare the effect of ICM^10^ and ICM^01^ versus BCM on reducing drop-out rates in apprentices enrolled in TDTP

3) To compare the effect of ICM^10^ and ICM^01^ versus BCM on reducing unemployment rates in apprentices enrolled in TDTP

4) To compare the effect of ICM^11^ versus ICM^10^ and ICM^01^ on reducing absenteeism in apprentices enrolled in TDTP

5) To compare the effect of ICM^11^ versus ICM^10^ and ICM^01^ on reducing drop-out rates in apprentices enrolled in TDTP

6) To compare the effect of ICM^11^ versus ICM^10^ and ICM^01^ on reducing unemployment rates in apprentices enrolled in TDTP

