## 14.1 Difference in proportion of AFDs

The sample size is fixed at approximately 448 individuals. We anticipate that the first few cohorts will be asked to pilot the screening tool, potentially removing up to 50 apprentices from the final sample size. We will use a fixed sample size of 400 apprentices, divided equally between Sudbury and Barrie sites. The expected cohort sizes will range from 6 to 10 apprentices, resulting in 20 to 34 cohorts per site. We will use a 3-level hierarchical design to model differences in proportion of AFDs where the daily attendance (Level 1) will be coded as binary; 0 for absence and 1 for attendance. Level 1 observations are clustered within individual apprentices (Level 2), which are nested within individual cohorts (Level 3). The sites (Sudbury and Barrie) and start date of cohort enrollment (q1 (January-March); q2 (April-June); q3 (July-Sept); q4 (Oct-Dec) and year) will be included as confounding variables in Level 1 and will not enter into the power calculations. Using this design, we performed a sensitivity analysis to determine the power to observe different primary outcome effect sizes with an $\alpha$-level 0.05**.**  As can be seen in the following table, even small differences in attendance (5% difference in proportions of AFDs) would still be detected with power ≥ 80% as long as the Level 2 inter-cluster correlation ≤ 0.125, a very reasonable assumption as there is no reason to believe that these apprentices’ attendance behaviours will be highly correlated with each other (23).

|  | **Scenarios**^1^ | | | | | | | |
| --- | --- | --- | --- | --- | --- | --- | --- | --- |
| **Variables** | 1 | 2 | 3 | 4 | 5 | 6 | 7 | 8 |
| Test Significance Level, α​ | 0.05 | 0.05 | 0.05 | 0.05 | 0.05 | 0.05 | 0.05 | 0.05 |
| Mean Difference, δ = µ₁ - µ₂​ | 0.1 | 0.15 | 0.05 | 0.05 | 0.05 | 0.05 | 0.05 | 0.1 |
| Standard Deviation, σ​ | 0.1 | 0.1 | 0.1 | 0.1 | 0.1 | 0.1 | 0.15 | 0.15 |
| Level 1 Unit Correlation, ρ₁​ | 0.75 | 0.75 | 0.75 | 0.75 | 0.75 | 0.75 | 0.75 | 0.75 |
| Level 2 Unit Correlation, ρ₂​ | 0.5 | 0.5 | 0.5 | 0.25 | 0.125 | 0.05 | 0.05 | 0.05 |
| Number of Level 3 Units in Group 1, C₁​ | 15 | 15 | 15 | 15 | 15 | 15 | 15 | 15 |
| Number of Level 3 Units in Group 2, C₂​ | 15 | 15 | 15 | 15 | 15 | 15 | 15 | 15 |
| Level 3 Units per Group Ratio, C₂/C₁​ | 1 | 1 | 1 | 1 | 1 | 1 | 1 | 1 |
| Number of Level 2 Units per Level 3 Unit, K​ | 6 | 6 | 6 | 6 | 6 | 6 | 6 | 6 |

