## 14.2 Difference in proportions of TDTP completion

Historical cohorts have demonstrated variation in program completion proportions but have been generally observed at a 75-80% graduation / completion rate. In this cluster randomized trial comparing the difference in proportions of TDTP completion, we define an *a priori* difference of ≥ 0.1 in completion proportions as the lower limit of a minimally significant difference (24). This is opinion-based on an informal survey of TDTP stakeholders. Given the same fixed sample and cohort size estimates discussed in Section 14.1, we performed a sensitivity analysis to determine the power to observe a difference in program completion proportions ≥ 0.1 using different control group completion rates with an $\alpha$-level 0.05**.**  As can be seen in the following table, a difference in completion proportions of 0.1 would be detected with power ≥ 80% as long as the control group completion proportion was ≥ 0.8, a reasonable assumption given the historically observed program completion proportions.

|  | **Scenarios**^1^ | | | | | | |
| --- | --- | --- | --- | --- | --- | --- | --- |
| **Variables** | 1 | 2 | 3 | 4 | 5 | 6 | 7 |
| Test Significance Level, α​ | 0.05 | 0.05 | 0.05 | 0.05 | 0.05 | 0.05 | 0.05 |
| 1 or 2-Sided Test?​ | Two | Two | Two | Two | Two | Two | Two |
| Control Group Proportion (p2)​ | 0.75 | 0.75 | 0.75 | 0.75 | 0.8 | 0.8 | 0.8 |
| Test Statistic under H0​ | 0 | 0 | 0 | 0 | 0 | 0 | 0 |
| Test Statistic under H1​ | 0.1 | 0.1 | 0.1 | 0.1 | 0.1 | 0.1 | 0.1 |
| Intracluster Correlation (ICC)​ | 0 | 0.05 | 0 | 0 | 0 | 0 | 0 |
| Clusters in Treatment Group (K1)​ | 20 | 20 | 33 | 25 | 20 | 33 | 25 |
| Clusters in Control Group (K2)​ | 20 | 20 | 33 | 25 | 20 | 33 | 25 |
| Cluster Ratio (K2/K1)​ | 1 | 1 | 1 | 1 | 1 | 1 | 1 |
| Cluster Sample Size in Treatment Group (M1)​ | 10 | 10 | 6 | 8 | 10 | 6 | 8 |
| Cluster Sample Size in Control Group (M2)​ | 10 | 10 | 6 | 8 | 10 | 6 | 8 |
| Cluster Sample Size Ratio (M2/M1)​ | 1 | 1 | 1 | 1 | 1 | 1 | 1 |
| Power (%)​ | 70.6 | 54.6 | 70.2 | 70.6 | 80.2 | 79.8 | 80.2 |

^1^ Highlighted cells (Yellow) represent changes from previous scenario

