#### 20.11b Program completion

We will use a logistic multivariate regression analysis to model program completion where the observation for program completion will be coded as binary: completion (=1) and drop-out (=0). The interventions (Distress thermometer and MH&A) will be included as well as a variable for their interaction effect. We will also include time period (year-quarter) and an interaction term between the time period and each intervention (Distress thermometer and MH&A). Clustered robust standard errors will be used to account for cohort intra-cluster correlation. Post-regression analyses using *margins* command will be used to estimate difference in program completion between treatment groups.

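### The power of at least 80% in Section 14.2 is for two groups of about 200, but the primary hypothesis compares single cells of about 100, where power is about 42–51% at best

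*Protocol*

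**What the plan says.** Section 14.2 sets the target: "we define an *a priori* difference of ≥ 0.1 in completion proportions as the lower limit of a minimally significant difference". Its table has seven columns, all two-sided at 5%, with 20 clusters of 10, 33 of 6 or 25 of 8 in each group. Power is 70.6%, 70.2% and 70.6% at control completion 0.75 with ICC 0, 54.6% at 0.75 with ICC 0.05, and 80.2%, 79.8% and 80.2% at 0.80 with ICC 0. The text concludes that "a difference in completion proportions of 0.1 would be detected with power ≥ 80" per cent if the control proportion is at least 0.80.

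On the sample, Section 14.1 says: "We will use a fixed sample size of 400 apprentices, divided equally between Sudbury and Barrie sites". Section 8 randomises cohorts 1:1 to the tool within site and makes the MH&A service available in Barrie only.

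On what is compared, hypothesis 6.1 states that "exposure to either the ICM^10^ or ICM^01^ models will be superior to the BCM model for reducing absenteeism", and it continues to drop-out and unemployment. Objective 2 in Section 7.1 reads: "To compare the effect of ICM^10^ and ICM^01^ versus BCM on reducing drop-out rates in apprentices enrolled in TDTP". Section 5.3 makes BCM the control for both single-intervention effects, and Section 20.1 compares the ICM arms with BCM. For the completion model, Section 20.11b says: "The interventions (Distress thermometer and MH&A) will be included as well as a variable for their interaction effect".

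Section 14.3 gives no calculation for employment. It says only that the differences are expected to resemble those for completion.

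**The concern.** BCM is one cell out of four. A table that uses all 400 apprentices as two groups cannot describe the contrast of one cell with another, yet that is the contrast in the primary hypothesis. The power claim is therefore attached to a comparison that the primary hypothesis does not make.

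The two power sections also do not match. Section 14.2 says it uses the sample and cohort sizes of 14.1, but the 14.1 table has 15 × 6 = 90 per group, close to one cell, while 14.2 has about 200, close to half the trial.

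At stake is how a null result is read. Someone relying on 14.2 would take a non-significant cell contrast as fair evidence against a 0.10 benefit, when the trial would miss such a benefit about half the time or more. The employment outcome leans on 14.2 and inherits the problem.

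**Working it through.** **Inputs.** Two-sided alpha 0.05, difference d = 0.10, control completion 0.75 or 0.80, ICC 0 or 0.05, cohorts of 6 to 10 (all Sections 14.1 and 14.2). Total 400, equal by site (14.1), and tool 1:1 within site (8), so 400/2/2 = 100 per cell. The 100 is inferred.

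**Formula.** Two-proportion z test, with n the effective number per group and K clusters of M:

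- n = K·M / (1 + (M − 1)·ICC)
- s0 = √[2·p̄(1 − p̄)/n], where p̄ is the mean of the two proportions
- s1 = √{[p1(1 − p1) + p2(1 − p2)]/n}
- power = Φ[(d − 1.96·s0)/s1]

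**Step 1: reproduce the table in 14.2.**

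| n per group | Proportions | Computed | Stated |
|---|---|---|---|
| 200 | 0.75 vs 0.85 | (0.10 − 1.96·0.0400)/0.0397 = 0.544, so 70.7% | 70.6% |
| 198 | 0.75 vs 0.85 | 70.3% | 70.2% |
| 200/1.45 = 137.9 | 0.75 vs 0.85 | 54.7% | 54.6% |
| 200 | 0.80 vs 0.90 | (0.10 − 1.96·0.0357)/0.0354 = 0.849, so 80.2% | 80.2% |
| 198 | 0.80 vs 0.90 | 79.8% | 79.8% |

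The table is therefore a calculation for 198–200 against 198–200.

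**Step 2: the same formula for one cell against BCM.**

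| ICC, cohort size | Effective n | 0.75 vs 0.85 | 0.80 vs 0.90 |
|---|---|---|---|
| 0 | 100 | 42.3% | 50.8% |
| 0.05, cohorts of 6 | 100/1.25 = 80 | 35.1% | 42.4% |
| 0.05, cohorts of 10 | 100/1.45 = 69.0 | 31.0% | 37.5% |

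For example, at n = 100 and control 0.75: (0.10 − 1.96·0.0566)/0.0561 = −0.194, and Φ(−0.194) = 42.3%.

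**Step 3: what a cell contrast can detect.** At n = 100 and ICC 0, 80% power is reached at a difference of about 0.150 (control 0.75) or 0.134 (control 0.80). For a difference of 0.10 it would take 250 or 199 per cell, that is 4 × 250 = 1000 or 4 × 199 = 796 apprentices.

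**Step 4: a contrast that does use all 400.** Average the tool effect equally over the sites: ½[(ICM10 − BCM) + (ICM11 − ICM01)]. Its variance is ¼·Σ p(1 − p)/n over the four cells, and power = Φ(0.10/SE − 1.96). The MH&A effect on completion is not in the protocol and is assumed here.

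| Base (BCM) | MH&A adds | ICC 0 | ICC 0.05, cohorts of 10 |
|---|---|---|---|
| 0.75 | 0 | SE 0.0397, 71% | 55% |
| 0.75 | 0.10 | SE 0.0350, 82% | 66% |
| 0.80 | 0 | SE 0.0354, 81% | 65% |
| 0.80 | 0.05 | SE 0.0326, 87% | 72% |

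**The case against.** Four points can be made for the plan.

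*The sample size is fixed by funding, and 14.2 is called a sensitivity analysis.* This is true, and a corrected figure changes no enrolment. But 14.2 still draws a conclusion about power for a primary outcome, and that conclusion does not fit the primary hypothesis.

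*Cell contrasts are a legitimate choice.* Section 5.3 deliberately makes BCM the control for each single intervention and names the interaction as a target. This stands. The error is in the power statement, not in the choice of contrast, so nothing here obliges the sponsor to replace the primary estimand.

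*The Barrie tool comparison is in the plan.* A reader might infer that it goes unused because it does not enter ICM10 vs BCM. The protocol does not support that: ICM11 vs ICM01 is in the secondary hypothesis (6.2), in objectives 4–6 under the Primary heading of 7.1, and in the factorial model. It only fails to contribute to the primary tool contrast.

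*The rows of 14.2 may describe something real.* A reader might infer that they belong to tool vs no tool alone. The groups are not named, and 20, 25 or 33 clusters per group also fit the 20 to 34 cohorts per site in 14.1, that is Barrie vs Sudbury. Either margin is possible; a cell contrast is not.

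It would also be too simple to call the tool coefficient in 20.11b the Sudbury effect. The model has tool-by-time terms as well, so the coefficient is the Sudbury effect in the reference year-quarter, and the plan reports differences through margins.

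**Conclusion.** Wrong as written. The power of at least 80% in 14.2 does not apply to the contrasts in hypothesis 6.1 and objectives 1–3. For those it is about 42–51% at ICC 0 and about 31–42% at ICC 0.05. The ICC 0 figures are a best case. The result assumes 100 per cell; modest imbalance between cells would not change the conclusion.

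The error reaches Section 14.3, which offers no calculation of its own. It does not show that the design is unusable or that the primary hypothesis must change. Nor would a site-averaged tool contrast restore the stated power under clustering: at ICC 0.05 with cohorts of 10 it also stays below 80%.

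**What to change.** **Required, wording only:**

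1. In 14.2, name the two groups that the existing rows describe, and say that they are a two-margin split of all 400 and not a cell contrast.
2. In 14.2, restate the power of ICM10 vs BCM and ICM01 vs BCM as about 42–51% at ICC 0 and about 31–42% at ICC 0.05, with detectable differences at ICC 0 of about 0.15 and 0.134.
3. Carry this into 14.3, and explain why 14.1 uses 90 per group when 14.2 claims the same sample.
4. Reconcile 6.2 and 7.1 on whether the ICM11 contrasts are secondary or primary.

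The cost is a few sentences and a lower stated power; no participants are added.

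**Optional:** pre-specify the site-averaged tool vs no-tool difference as a margins contrast from the 20.11b model. It uses all 400 and both randomised tool comparisons. State its power at both ICCs, with the assumed MH&A effect: about 71–82% (base 0.75, MH&A adding 0–0.10) and 81–87% (base 0.80, MH&A adding 0–0.05) at ICC 0, and about 55–66% and 65–72% at ICC 0.05 with cohorts of 10. The price is that it averages the tool effect with and without the MH&A service. It also leaves the ICM01 vs BCM hypothesis untouched, which must keep its own contrast and its lower power.

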## 14.3 Difference in proportions of full-time employment

Differences in full-time employment proportions between the groups is expected to be similar to differences in proportions of TDTP program completion.

# 15 Recruitment

To be eligible for TDTP enrollment, individuals must be Canadian, female, black, from a racialized community, an immigrant, and/or Indigenous. Eligible individuals must submit to an interview with Community Builders®. Successful candidates must demonstrate that they are a good fit for the TDTP by showing, at a minimum, an interest in the construction trades and possessing some basic English or French-speaking and writing skills. Enrollment in the TDTP is not contingent on eligible individuals agreeing to participate in the TeachMeToBuild study. Individuals enrolled in the TDTP whose cohort is randomized to the Distress Thermometer screening tool intervention will be introduced to the TeachMeToBuild study during their initial TDTP orientation. The case managers will use the expressed consent powerpoint presentation to introduce the study to the students. During this introduction, all TDTP students will be informed that their participation in the study is voluntary and refusal to enrol or withdraw after study enrollment will not affect their subsequent TDTP participation or outcomes. After this introduction, each individual will be provided with the contact information (email and telephone number) for a study team member that can be reached to further discuss the study and possible enrollment. For those individuals who contact the study team member, an in-person meeting or audio/video teleconference will be scheduled. During this meeting, the study team member will discuss the study rationale, objectives, participant responsibilities, data collection, risks and benefits. During this meeting, the study team member will encourage and answer study-related questions. For interested individuals, the study team member will review the informed consent form (ICF) and answer all questions. Interested individuals will be provided with a paper/electronic copy of the ICF to review, and a subsequent follow-up in-person or audio/video teleconference meeting in 72 hours (business days) will be scheduled between the study team member and the interested individual to determine their interest to enroll in the TeachMeToBuild study. All TDTP students will be reminded by the study team member during the meetings that study participation is voluntary and refusal to enrol or withdraw after study enrollment will not adversely affect their subsequent TDTP participation or outcomes. To withdraw from the study, the participant will inform the case manager who will then inform the study team members.

Potential study participants will be offered several incentives to enroll in the study. Each study participant will be provided with a tablet computer for the duration of the 12-week TDTP to facilitate their daily entries in the Distress Thermometer screening tool. These tablet computers will be provided free-of-charge. Study participants will not be responsible for the costs associated with any lost, stolen or damaged units. These tablet computers must be returned to Community Builders® at the end of the 12-week TDTP. Study participants who complete ≥ 90% of their daily Distress Thermometer screens will receive $50 for their time and effort and be enrolled in a draw for 5 tablet computers to be awarded at the end of the TeachMeToBuild study.

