# 10 Eligibility

Participants must provide written, informed consent before any study procedures occur.

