## 16.2 Concealment mechanism

The random allocation sequence will be generated using the *ralloc* function in STATA 17/MP for Mac. This allocation sequence will be uploaded into the Royal Victoria Regional Health Centre Research Electronic Database Capture (REDCap®) system (25,26), which is an online, password-protected, web-based research electronic database system stored on the Personal Health Information Protection Act (PHIPA) (27)-protected servers at the Royal Victoria Regional Health Centre. An independent study coordinator not associated with the TDTP will be responsible for accessing the password-protected allocation sequence from REDCap®. Only the study coordinator will have access to the allocation sequence to avoid any influence from the study investigators, TDTP Training Program Coordinator, or other personnel. Allocation concealment will be ensured as the study coordinator will not release the randomisation code until each cohort has completed registration of all of its TDTP students.

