## 16.3 Implementation

Cohort randomization will be requested by the TDTP Training Program Coordinator from the independent study coordinator (Section 16.2) 1 week prior to that cohort’s TDTP start date by calling a centralized study telephone number. The study coordinator will access the random allocation sequence through REDCap®, and then inform the Training Program Coordinator of the allocation for the cohort. The Training Program Coordinator will provide this allocation information to the TDTP students. Informed consent from each interested TDTP student in the randomized cohorts ICM^1x^ will then be obtained by *TeachMeToBuild* study personnel (Section 15).

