### 18.12 Routinely collected data

Any clinical encounters with a healthcare provider for any reason may require the collection of personal health information, such as Ontario Health Insurance Plan number, along with other information as dictated by the healthcare provider, healthcare facility, and diagnostic and therapeutic care plan. The PHIPA-compliant storage and transmission of this routinely collected clinical data will be the responsibility of the health information custodian. This study has no requirements for the *a priori* collection of any routinely collected clinical data.

Other routinely collected data specific to the TDTP includes daily attendance and program completion. The Training Program Coordinator is responsible for this data collection. The daily attendance data will be collected using the Distress Thermometer screening tool. Program completion data will be collected at the end of the 12-week TDTP and entered into the electronic case report form in REDCap by study personnel.

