All demographic data (Section 18.11) will be entered electronically by apprentices into REDCap through a secure survey link that will be sent by email upon registration in the Distress Thermometer screening tool. A unique study number will be assigned to each apprentice in REDCap. This unique study number, along with the patient’s name (first, middle, last), Ontario Health Insurance Plan number, date of birth, and unique electronic health record system number (if applicable) will be stored in a password-protected EXCEL computer file. This study EXCEL file will be stored in a dedicated, password-protected electronic shared drive located on the Royal Victoria Regional Health Centre Personal Health Information Protection Act (PHIPA)-compliant servers. This EXCEL file will permit linkage to the electronic case report form to enable study personnel to record outcome data over the study period for a participant. Real-time data quality rules will be implemented in REDCap that will display warning pop-up messages whenever the rules are violated during data entry. These quality rules will minimize missing values in required fields; prevent incorrect data type entry and out of range data entry; identify outliers for numerical fields; and prevent invalid data entry into multiple choice fields. The data quality rules will also be available to be executed at any time by a study monitor or study personnel. All electronic case report form entries and edits are associated with an electronic audit trail that identifies the user, date and time of entry, and entry type. The type of activity that study personnel may undertake in REDCap is regulated by privileges associated with their user identification and password. Incremental data back-ups of REDCap are routinely performed twice a day, with off-site storage of the backed-up files done on a monthly basis.

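### Study approach and consent are described for tool cohorts only, after allocation is known: this contradicts other sections, leaves controls without a follow-up route and opens the tool comparison to selection

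*Protocol*

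**What the plan says.** **Who is approached and when.** Protocol section 15 limits the introduction to the tool arm: "Individuals enrolled in the TDTP whose cohort is randomized to the Distress Thermometer screening tool intervention will be introduced to the TeachMeToBuild study". Consent is opt-in. Students receive a contact address, only those who make contact are given a meeting, and a second meeting follows after 72 hours (business days). Section 16.3 gives the order of events. First, "The Training Program Coordinator will provide this allocation information to the TDTP students". Then, "Informed consent from each interested TDTP student in the randomized cohorts ICM^1x^ will then be obtained by" study personnel. ICM1x means the two tool cells, ICM10 and ICM11. The concealment rule in section 16.2 withholds the code only "until each cohort has completed registration of all of its TDTP students". It therefore protects entry to the training program, not later entry to the study.

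**Who must consent.** Section 10: "Participants must provide written, informed consent before any study procedures occur". No exemption or waiver is stated for BCM or ICM01 cohorts. Section 26 says that all eligible participants are informed by their case managers, and section 34 costs consent and enrolment at 800 hours, 2 hours per person.

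**How data arrive.** Section 18.12: "The daily attendance data will be collected using the Distress Thermometer screening tool". Section 19 sends the demographics survey link "upon registration in the Distress Thermometer screening tool". Section 12.24 has case-management hours recorded in the tool. Section 12.13 takes 24-month employment from the graduate's own report and asks consent to check it with the employer. Section 11.12 issues tablets for the tool to ICM10 and ICM11 apprentices.

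**The concern.** In a cluster-randomised trial with individual consent, the clusters are comparable by design, but the people analysed are comparable only if recruitment works the same way in every arm. Here the operative sections describe recruitment in one arm of the tool comparison, after students know what they have been allocated, through a process that requires the student to seek out the study team. Apprentices who do so are plausibly the more engaged ones, and engagement is close to what attendance and completion measure.

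Two things are at stake. Control apprentices who are never approached cannot readily be asked about employment two years later, and they may not receive the demographics link. And if the tool arm consists of consenters while the control arm consists of everyone enrolled, the tool effect is mixed with self-selection.

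**Working it through.** **1. Sections side by side: who is consented?**

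- Tool cohorts only: section 15 (introduction), section 16.3 (consent). Section 15 also describes every study participant as receiving a tablet for daily screening.
- Everyone: section 10 (written consent required of participants), section 26 (all eligible participants informed).
- Timing: section 13 puts cohort randomisation at day -7 and consent at day 0, in line with section 16.3.

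The budget in section 34 points both ways:

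- Consent: 800 h / 2 h = 400 people, the whole sample in section 14.1.
- Cash incentive: 10 000 / 50 = 200 people, which is the tool half of 400 under the 1:1 allocation in section 8.

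The incentive is tied to completing tool screens, so 200 is natural there. The figure of 400 consents is not compatible with sections 15 and 16.3.

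**2. Data route for control cohorts, by outcome**

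- *Attendance:* entered in the tool, but described in section 18.12 as routine program data and documented by staff (section 12.11). The staff-entered fields in section 18.11 include attendance. Control data need not be missing.
- *Completion:* routine, entered in REDCap by study personnel (section 18.12). Need not be missing.
- *Employment at 24 months:* needs contact with the graduate. No route is described for controls.
- *Demographics:* link sent on registration in the tool. No route is described for apprentices who are not registered.
- *Foundational skills:* collected from each apprentice at routine orientation (section 18.13a). Available in all arms.

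**3. The plan's own benchmark**

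Section 14.2, scenario 5: 20 clusters of 10 per arm (n = 200), 0.80 vs 0.90, ICC 0, two-sided alpha 0.05, stated power 80.2%. With pooled variance under the null:

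Φ[(0.10 − 1.96·√(2·0.85·0.15/200)) / √((0.90·0.10 + 0.80·0.20)/200)] = Φ(0.849) = 80.2%.

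This reproduces. The target difference is therefore 10 points with about 200 apprentices per arm.

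**4. Selection bias if only consenters are analysed in tool cohorts**

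Assumptions, not in the protocol: true completion 80% in both arms, no tool effect, refusal fraction r, completion c among refusers, all controls counted.

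Bias = (0.80 − r·c)/(1 − r) − 0.80

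- r = 0.10, c = 0.50: 0.75/0.90 − 0.80 = +0.033
- r = 0.20, c = 0.60: 0.68/0.80 − 0.80 = +0.050

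These are one third and one half of the 10-point target.

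**5. Effect on false-positive risk (clustering ignored)**

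SE = √(p(1−p)/n₁ + 0.80·0.20/200), where p is completion among consenters and n₁ = 200(1 − r). Type I error = P(|Z + bias/SE| > 1.96).

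- r = 0.10, c = 0.50: p = 0.833, n₁ = 180, SE = 0.0396, ratio 0.84, type I error 13.4%
- r = 0.20, c = 0.60: p = 0.85, n₁ = 160, SE = 0.0400, ratio 1.25, type I error 24.0%

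The range is wide. Write the bias as (1 − consent rate) × (completion gap between consenters and refusers):

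| Consent rate | Gap | Bias | Type I error |
| --- | --- | --- | --- |
| 90% | 10 points | 1 point | 5.7% |
| 70% | 10 points | 3 points | 10.9% |
| 70% | 20 points | 6 points | 31.3% |
| 50% | 20 points | 10 points | 67.9% |

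**6. The same calculation under section 12.12**

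Section 12.12 divides drop-outs by all apprentices enrolled in the program. Refusers then stay in the tool arm and the bias for completion is zero. The obstacle is section 10: the use of data from refusers and unapproached controls needs a consent basis, and none is stated.

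**The case against.** The strongest reply is that the harm depends on an analysis the protocol does not prescribe. The completion denominator is all enrolees, attendance and completion are routine staff-recorded data, and section 26 together with the 400-person consent budget suggests that every cohort was meant to be approached. The analysis set may also be settled in a statistical analysis plan.

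Much of this stands, and it limits the point in four ways:

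- A reader might infer that control outcomes are missing altogether. The documents do not support that. Restricting apprentice tablets to tool cohorts does not bar staff from entering control attendance or hours. Foundational skills are collected from everyone, and section 19 sends survey links to each apprentice. Section 18.14 describes health-data linkage that does not rest on individual consent, although it still needs each person's health insurance number.
- A reader might infer bias on every primary outcome. That is not shown. Employment is counted among graduates only (section 12.13), so the completion formula does not carry over, and nothing was calculated for attendance.
- A reader might add bias from apprentices who leave before the consent meeting. Section 13 places consent at day 0, before the first program day, so the schedule does not establish such a window.
- The refusal and completion rates used here, and the direction of the bias, are assumptions.

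What the reply does not answer is the contradiction itself. Section 26 and the budget conflict with sections 15 and 16.3 without overriding them. An analysis plan cannot supply employment data from people who were never asked, nor reliably undo self-selection after allocation.

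**Conclusion.** The point holds as an internal contradiction with two consequences.

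First, the operative text gives no consent or contact route for BCM and ICM01 apprentices. The outcomes most exposed are 24-month employment and the demographics that depend on registration in the tool.

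Second, for attendance and completion the risk is post-allocation selection. It is conditional: it arises if consenters in tool cohorts are compared with all enrolled controls, and for completion it vanishes under the section 12.12 denominator once a consent basis is stated. On the assumed inputs it amounts to +3.3 to +5.0 points of completion with no true effect, against a target of 10. The size is illustrative; the contradiction between the sections is certain. It should be resolved before enrolment, because the approach to controls cannot be repaired afterwards.

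**What to change.** Reconcile sections 10, 12.12, 15, 16.3, 18.12, 19, 26 and 34 as follows.

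- **Approach and consent (15, 16.3, 26).** Introduce the study and seek consent in the same way in all cohorts, before students are told the allocation. Include consent for employment follow-up and data linkage.
- **Data route (12.24, 18.12, 19).** Send the demographics and exit surveys to all cohorts by a route that does not depend on registration in the tool. Have staff record attendance and case-management hours in the same way in every cohort.
- **Analysis population.** Analyse attendance and completion by randomised cohort, in one of two sets stated in advance: all program enrolees from routine records, with an ethics-approved consent basis or waiver; or all apprentices consented before allocation is disclosed. The first keeps the section 12.12 denominator. The second would require that denominator to be amended.

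**Cost.** A protocol and consent-form amendment, and tighter scheduling between registration and program start. Consent time for 400 people is already budgeted, as is survey time (400 h at 1 h each). One weakness remains: the coordinator would still know the allocation a week before the start, and the trial is open-label, so the introduction given to students should follow a fixed script.
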